**Fig. 2 Fig2:**
[figure not shown]
Conceptual Model of the RMA Intervention

#### District randomization, village selection, and randomization

The Ministry of Health chose the Dosso region of Niger for the RMA intervention. This region has five districts from which three districts, Dosso, Doutchi, and Loga, were selected for participation. Based on the logistical challenges of providing all RMA intervention approaches in each district, each district was randomly assigned to one of the three intervention approaches (home visits alone, small groups alone, or a combination), with controls selected across all three districts. Based on power analyses (described below), the minimum number of clusters in each of the four arms was 12, requiring inclusion of 16 villages across each of the three districts (12 intervention and 4 control). Village selection and randomization followed a multi-stage process whereby eligible villages in the three districts were first identified based on the following criteria: 1) rural (i.e., not designated as a market town or city), 2) Hausa- or Zarma-speaking, 3) a minimum of 1000 inhabitants, and 4) located within 5 km of a *centre de santé intégré* (CSI) or *case de santé* (CS) health facility. There were 101 villages in Dosso, 110 in Doutchi, and 36 in Loga that met these criteria. From the eligible villages, we then stratified villages based on three level of health service provision: 1) villages with CSIs, larger health facilities serving multiple villages where doctors, nurses, and midwives provide the full contraceptive method mix and related counseling; 2) villages with CSs, village-level facilities where community health agents provide a subset of contraceptive methods; and 3) villages with neither CSI nor CS. Among the 247 total eligible villages across the three districts, 21% had a CSI, 56% had a CS, and 23% had neither. In order to select a sample of villages within each district that was representative of the distribution of health facilities across the region, we randomly selected nine villages with a CS, three with a CSI, and four with neither in each of the three districts. To create a control arm representative of villages in each district, and that included representation of all levels of health facility, we randomly assigned four of the total 16 villages per district to the control condition, consisting of two villages with a CS, 1 with a CSI, and 1 with neither. The remaining 12 villages were assigned to the intervention condition assigned to that district (see Fig. 3).

**Fig. 3 Fig3:**
[figure not shown]
Selection and Randomization Procedures

##### Additional randomization for the 40-month follow-up

Prior to the 40-month follow up, six intervention villages per district will be randomly assigned to continue to receive supervision from Nurse Supervisors while the remaining six intervention villages in each district will continue intervention activities with no supervision. Pairwise (block) randomization within each intervention arm by current modern contraceptive use rate will be conducted to ensure similar distributions of modern contraceptive utilization in those villages continuing vs ceasing supervision. All four control villages in each district will continue to serve as controls. This additional randomization will allow us to determine sustainability of the effects of the intervention without direct supervision.

#### Power

Power calculations for our study were conducted a priori based on our primary outcome of interest, modern contraceptive method use (reported by the adolescent wives in our sample). We used pairwise tests for time by treatment effects comparing each intervention group individually to the control group. We chose to account for a moderate intra-cluster correlation coefficient – kappa = 0.05 and an attrition rate of 10%. We also chose to account for the ability to detect an effect size of 2.0 greater odds of contraceptive method use, based on literature reviews of evaluations of interventions seeking to improve contraceptive use, as well as our own experience conducting such trials in other regions. Four arms with 12 clusters nested within each arm, and a sample size of 240 couples per arm (300 couples at baseline with 20% expected attrition; 1200 total baseline participating couples) was calculated to provide 80% power to detect associations of this magnitude.

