## Background

Recent Demographic and Health Survey (DHS) data from Niger show that 76% of girls marry before the age of 18 and 28% before the age of 15 [1]. Though marrying under age 18 years is permitted by law (legal age of marriage is 15 years for girls) [2], child marriage is associated with poor adolescent health and development, including neonatal and maternal mortality, lack of formal education, and intimate partner violence (IPV). Child marriage is also associated with early childbearing and high adolescent fertility in Niger and multiple other contexts [3–5]. Approximately 9% of girls give birth to a child before age 15 years and 42% give birth between ages 15 and 18 years in this West African nation, [6] with adolescent and total fertility in Niger higher than any country globally [7].

Girls who marry at younger ages in Niger are less likely than those marrying at older ages to utilize maternal health care services (e.g., antenatal visits and institutional delivery), contributing to poor health outcomes [8]. In 2012 in Niger, only 7% of all 15–19 year-old married adolescents (male and female) reported use of a modern contraceptive method [9]. Barriers to modern contraceptive use include lack of access, lack of awareness, misinformation and lack of knowledge, and opposition to use by partners and family [9]. Multiple social norms (i.e., shared social expectations) have been documented in this and other sub-Saharan cultural contexts that additionally impede modern contraceptive uptake [10]. Programs designed to combat early and frequent childbearing in these regions by promoting modern contraceptive use face the challenge of addressing these many barriers.

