##### Baseline data

At baseline, 1314 husbands and 1315 adolescent wives were contacted to participate in the study. Of these, 1156 and 1157, respectively, met inclusion criteria, consented to participate, and provided survey data, resulting in a baseline participation rate of 88% for both males and females. Upon review, data from 51 husbands and 60 adolescent wives were removed as a result of being highly incomplete or with data quality concerns. This left 1105 husbands and 1097 adolescent wives in our analytic sample. However, the leaders of one village decided post-baseline to discontinue participation in the study, requiring that data from this village be removed, resulting in a final analytic sample of 1080 men and 1072 women.

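### The power paragraph uses two attrition rates, and its 80% power for an odds ratio of 2.0 is not supported at the only use rate the article reports (7%) unless correlation over time is high

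*Protocol article*

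**What the plan says.** All planning figures stand in one paragraph of the protocol article, under Power.

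- Clustering and loss: "kappa = 0.05 and an attrition rate of 10" per cent.
- Effect: "an effect size of 2.0 greater odds of contraceptive method use".
- Test: "We used pairwise tests for time by treatment effects comparing each intervention group individually to the control group".
- Size: "Four arms with 12 clusters nested within each arm, and a sample size of 240 couples per arm", explained in brackets as "300 couples at baseline with 20% expected attrition; 1200 total baseline participating couples".
- Claim: this "was calculated to provide 80% power to detect associations of this magnitude".

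The paragraph names no control-group use rate, alpha or correlation between survey rounds. The Background reports that in 2012 only 7% of 15–19-year-old "married adolescents (male and female) reported use of a modern contraceptive method"; the Abstract repeats the figure. No other use rate appears. Under Contraceptive method use, women pregnant at the survey are left out of the primary analysis. Under Baseline data, one village withdrew after baseline, "resulting in a final analytic sample of 1080 men and 1072 women".

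**The concern.** Two values are given for one parameter of one calculation, so a reader cannot tell which calculation produced the 80%. Power for a fixed odds ratio also depends strongly on the control rate. At a low rate, an odds ratio of 2.0 is a small absolute difference, and 12 villages per arm with this intra-cluster correlation carry limited information about it.

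The Discussion says the results will go to the Ministry of Health to inform decisions on scaling. If an arm shows no clear effect and the reader trusts 80% power, that result will count against the intervention more heavily than the design may warrant.

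**Working it through.** **Attrition.** 300 × 0.80 = 240 and 300 × 0.90 = 270. The stated 240 follows from 20% only.

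**Inputs for power.** From the Power section: 240 per arm in 12 villages (20 per village), intra-cluster correlation (ICC) 0.05, odds ratio 2.0. From the Background: 7%, used here as the control rate. Assumed: two-sided alpha 0.05, and the correlations over time, which are varied.

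**Effect at 7%.** Odds 0.07/0.93, doubled, give a rate of 0.1308, a difference of 0.0608. Binomial variances: a = 0.07 × 0.93 = 0.0651; b = 0.1308 × 0.8692 = 0.1137.

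**Comparison at follow-up.**
- Design effect 1 + 19 × 0.05 = 1.95; effective n = 240/1.95 = 123 per arm.
- SE = √[(0.0651 + 0.1137)/123] = 0.0381; z = 0.0608/0.0381 = 1.60; power = Φ(1.60 − 1.96) = 36% (35% with pooled variance).
- With 270 per arm: design effect 1 + 21.5 × 0.05 = 2.075, effective n 130, power 37%.
- Ignoring clustering altogether: about 60%.
- Over all control rates, the maximum with 240 per arm is 78%, near a control rate of 41%. With 270 per arm it is 80.2%.

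**Time-by-treatment test (the stated one).** Let c be the correlation of village effects between rounds and r the within-person correlation. For an arm with variances v0 and v1 at the two rounds, the variance of the mean change is

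ICC × [v0 + v1 − 2c√(v0·v1)]/12 + (1 − ICC) × [v0 + v1 − 2r√(v0·v1)]/240.

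Control has v0 = v1 = a. Intervention has v0 = a and v1 = b. The two arms are summed.

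- c = 0.5, r = 0.1: control 0.000271 + 0.000464; intervention 0.000387 + 0.000640; SE 0.0420; z = 1.45; power 31%.
- c = 1.0, r = 0.5: control 0 + 0.000258; intervention 0.000028 + 0.000367; SE 0.0256; z = 2.38; power 66%.
- c = 1.0, r = 0.65: SE 0.0218; z = 2.80; power 80%.
- c = 1.0, r = 0.5, control rate 12% (21.4% under the odds ratio, difference 0.0943): SE 0.0317; z = 2.97; power 84%.

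**How high is 0.65?** For two yes/no measures whose odds differ by a factor of 2, the correlation cannot exceed √(1/2) = 0.71. In the intervention arm, r = 0.65 with c = 1.0 implies an overall correlation of 0.05 + 0.95 × 0.65 = 0.67, close to that ceiling, for use reported 24 months apart.

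**Detectable odds ratio at 7% with 80% power.** 3.07 for the follow-up comparison; 2.72 for the time-by-treatment test with c = 0.8 and r = 0.3.

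**The case against.** A reader might infer that 80% power cannot be reached at all. The documents do not support that. The follow-up figures, including the 78% ceiling, belong to a comparison that is not the stated test, and even that ceiling becomes 80.2% at the printed 10% attrition. The stated test can reach 80% at 7% if correlation over time is high enough. The Data analysis section plans nested random effects; if that means a constant village intercept, village autocorrelation is 1.0, the favourable end of the range. The low end rests on values the article does not give.

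Nor is 7% declared as the planning rate. It is a 2012 figure for both sexes. The trial outcome excludes pregnant women, counts lactational amenorrhoea, is measured in villages within 5 km of a health facility, and is taken when participants are at least two years older. Any of these could move the rate, and a modest rise matters: 84% at 12% with correlations 1.0 and 0.5, and 94% at 20%.

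A condensed article may also leave alpha, control rate and correlation to a fuller document, so their absence alone is not the fault.

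A reader might also count the lost village and the 1072 women as errors in the calculation. They are not: the calculation was made in advance and the losses are openly reported. Their effect also depends on the disputed rate: 1072 × 0.80/4 = 214 per arm, but 1072 × 0.90/4 = 241.

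What remains is a plain contradiction on attrition, and a power figure that falls well short at the only rate the article offers unless unstated inputs are favourable.

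**Conclusion.** The concern holds in this limited form. The attrition rates contradict each other; that is certain, but small in effect (36% against 37% power for the follow-up comparison). The larger point is that 80% power is not supported at 7% use: about 36% for a follow-up comparison, and about 31% to 66% for the time-by-treatment test over the correlations examined. At that rate 80% needs a within-person correlation of about 0.65 with village autocorrelation 1.0. Excluding pregnant women reduces the analysed number further; the article gives no figure from which to size this. The result assumes two-sided alpha 0.05, the stated intra-cluster correlation, 20 analysed women per village, and 7% as the control rate. The claim is unsupported as written, not shown to be impossible.

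**What to change.** 1. State one attrition rate and make the sample size agree with it: 240 per arm at 20%, or 270 at 10%.
2. State the control rate, alpha (with sidedness) and correlation over time that gave the 80%.
3. Restate the power, or the minimum detectable odds ratio, for the time-by-treatment test at the observed baseline use rate and with the non-pregnant denominator.
4. As context for reading a null result, give the same figure for the 47 villages (48 less the one that withdrew) and 1072 women retained, labelled as separate from the advance calculation.

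The cost is a re-run of the calculation and a few revised sentences. No participants are added. The stated power may become less favourable.

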#### Primary outcome measure

##### Contraceptive method use

The main outcome of interest for the RMA intervention and evaluation is modern contraceptive method use as reported by the married adolescent wife participants. Current modern contraceptive use will be assessed using data from the following survey items adapted from the DHS [19]: 1) “Are you or your husband currently doing something or using any method to space or delay pregnancy?” 2) if yes, “which method are you currently using?” Thus, if a married AGYW participant responds that, yes, they or their husband are currently using a modern method (IUD, injectable, implant, pill, condom, female condom, emergency contraception, or LAM) they will be considered current modern contraceptive method users. Women pregnant at the time of the survey will be excluded in analyses of this outcome.

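### The 240 couples per arm behind the 80% power allow for attrition only, but the primary analysis also drops women pregnant at the survey, so fewer than 240 wives per arm are evaluable

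*Protocol article*

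**What the plan says.** The Power section of the protocol article says the calculation was "based on our primary outcome of interest, modern contraceptive method use (reported by the adolescent wives in our sample". The test is described as follows: "We used pairwise tests for time by treatment effects comparing each intervention group individually to the control group". The target is the "ability to detect an effect size of 2.0 greater odds of contraceptive method use". The inputs include a "moderate intra-cluster correlation coefficient – kappa = 0.05 and an attrition rate of 10" per cent. The resulting size is "a sample size of 240 couples per arm (300 couples at baseline with 20% expected attrition; 1200 total baseline participating couples", with 12 villages in each arm, and this "was calculated to provide 80% power to detect associations of this magnitude".

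The definition of the same outcome, under Primary outcome measure, ends: "Women pregnant at the time of the survey will be excluded in analyses of this outcome".

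Three other places show that this exclusion will remove records:

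- The six eligibility criteria for wives, under Recruitment and eligibility, do not mention pregnancy, so pregnant wives can enrol.
- The intention measure has its own survey item for respondents who are currently pregnant, so they are expected among those surveyed.
- The Data analysis section rules out imputation, so excluded records are not replaced.

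The Power section does not mention pregnancy, and the article gives no expected pregnant share.

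**The concern.** The Power section and the outcome definition describe different analysis sets for one test. The power statement credits the test with every retained wife. The outcome definition analyses only retained wives who are not pregnant at the survey. The article's Background describes very high adolescent fertility ("42% give birth between ages 15 and 18 years in this West African nation"), so the excluded group is unlikely to be negligible.

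The power statement tells readers how to take a non-significant arm. Three pairwise comparisons are meant to inform the Ministry of Health's decision on scaling up. If the 80% describes a larger set than the one analysed, a null arm could be taken as better evidence of no effect than it is. The planning use rate adds to the problem. The Power section states neither the rate nor its denominator, so a reader cannot tell whether the 80% was worked out for all wives or for non-pregnant wives.

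**Working it through.** **Inputs from the article.** 300 couples per arm at baseline; 20% attrition attached to that figure; 12 villages per arm; ICC 0.05; odds ratio 2.0; power 80%.

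**Assumed, because not stated.** Two-sided alpha of 0.05; share pregnant at the survey f = 10% or 20%; control use rates between 7% and 40%. The 7% is the Background figure for married adolescents aged 15–19.

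**Step 1. Reproduce the plan's number.** 300 × (1 − 0.20) = 240 per arm, or 20 per village. Attrition accounts for the whole reduction.

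**Step 2. The stated 80%.** It cannot be reproduced, because alpha, sidedness, control rate and within-woman correlation are not given. It is taken at face value, as a noncentrality of 1.960 + 0.842 = 2.802 at 240 per arm.

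**Step 3. Evaluable wives.** n = 240 × (1 − f).

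- f = 10%: 216 per arm, 18 per village.
- f = 20%: 192 per arm, 16 per village.

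**Step 4. Power if the planning rate already refers to non-pregnant women.** The use rate does not change; only n does. The design effect is 1 + (m − 1) × 0.05, with m wives per village, and effective n = n / design effect.

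- m = 20: design effect 1.95, effective n = 123.1.
- m = 18: design effect 1.85, effective n = 116.8. Noncentrality 2.802 × √(116.8/123.1) = 2.729, power 77.9%.
- m = 16: design effect 1.75, effective n = 109.7. Noncentrality 2.802 × √(109.7/123.1) = 2.645, power 75.3%.

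If stable village effects cancel in the time-by-treatment contrast, the noncentrality scales with √(1 − f). Power is then 75.7% at 10% and 70.7% at 20%.

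**Step 5. Power if the planning rate refers to all wives and pregnant women are non-users.** Excluding them raises the control rate among those analysed from p to p/(1 − f). With odds ratio 2.0 in the analysed women and p₂ the matching intervention rate, the variance of the log odds ratio per effective woman is V = 1/[p(1 − p)] + 1/[p₂(1 − p₂)]. The noncentrality from step 4 is multiplied by √(V before / V after).

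Example: p = 7%, f = 20%. The control rate becomes 0.07/0.80 = 8.75%. V falls from 24.15 to 19.93, a factor of 1.101. Noncentrality is 2.645 × 1.101 = 2.912, power 82.9%.

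| Control rate, all wives | ICC 0.05: f = 10% / 20% | Village effects cancel: f = 10% / 20% |
|---|---|---|
| 7% | 81.5% / 82.9% | 79.5% / 78.8% |
| 20% | 80.3% / 80.3% | 78.3% / 76.0% |
| 25% | 79.8% / 79.1% | 77.7% / 74.7% |
| 40% | 77.8% / 74.1% | 75.6% / 69.5% |

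The evaluable number falls in every case. Power at low use rates may rise or fall slightly, and at higher rates it falls.

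**The case against.** The strongest counter-argument is that a smaller n need not mean less power. If pregnant women are nearly all non-users, removing them leaves the number of users almost unchanged, and at low use rates the users carry most of the information about an odds ratio. Step 5 bears this out. A reader might infer that the exclusion must lower power. The article does not support that, because it gives neither the planning rate nor its denominator.

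The second argument is that the Power section gives two attrition figures, 10% among the inputs and 20% beside the sample size, and the gap could hold an allowance for pregnancy. With 10% attrition, 270 remain, and up to 1 − 240/270 = 11% could be pregnant before the number falls below 240. At 10% pregnant, 243 remain and power is 80.2% on the step 4 basis. That arithmetic is right, but the text labels the whole 20% as attrition and assigns none of it to pregnancy. The reported baseline sample leaves little room either: 1072 women is 268 per arm on average, and 20% attrition brings that to about 214 before any pregnancy exclusion.

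Two further readings are tempting and should not be made:

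- **A minimum pregnant share from the Background figures.** Counting nine months per birth gives 0.42 × 0.75 / 4 / 0.76 = 10.4%, or 13.8% over three years. Counting only six identifiable months gives 6.9% to 9.2%. The figures cover ages 15–18, while the wives were 13–19 at baseline and are older at follow-up. These are assumptions, not a lower bound.
- **Loss of a woman's whole contribution if she is pregnant at one survey.** There are three surveys, and the planned mixed models can use the observations that remain.

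It is also fair to say that the uncheckable 80% is a larger uncertainty than two to five points.

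**Conclusion.** The mismatch stands. The 240 per arm is the number retained after attrition, not the number evaluable for the primary outcome. At assumed pregnant shares of 10% and 20%, the evaluable number is 216 and 192.

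The consequence for power is conditional. All figures take the stated 80% as correct and assume two-sided 0.05.

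- **Planning rate for non-pregnant women:** about 78% / 75% with ICC 0.05, or about 76% / 71% if village effects cancel.
- **Planning rate for all wives, with pregnant women non-users:** about 80–83% with ICC 0.05, and about 76–80% if village effects cancel, at control rates of 7–20%.

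A reader might conclude that the trial is materially underpowered because of this exclusion. The article does not establish that. It establishes that the stated analysed size is one the design does not deliver, and that the 80% cannot be interpreted until the denominator of the planning rate is given.

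**What to change.** In the Power section:

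1. Replace 240 with the number expected to be evaluable for the primary outcome: 300 × (1 − attrition) × (1 − share pregnant at the survey). Use one attrition rate, after reconciling the 10% and the 20%, and take the pregnant share from the baseline survey already collected.
2. State the planning use rate for non-pregnant wives, the population that the primary analysis uses.
3. Restate the power, or the detectable odds ratio, for the time-by-treatment test on that number and rate.

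The cost is one recalculation and a few sentences. No further enrolment or data collection is needed. The downside is that the stated power may become less favourable.

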#### Participants – recruitment, eligibility, consent, and ethics

##### Recruitment and eligibility

At baseline, participants were selected for recruitment based on a complete listing of married AGYW and their husbands provided by leaders in each of the participating villages. A random numeric sequence was attached to the listing and those couples numbered 1–25 were selected for recruitment. These households were then approached by trained male and female research assistants (RAs) fluent in both French and Hausa and/or Zarma accompanied by a village guide (appointed by the village leaders) to determine interest in participating in the study. If more than one adolescent wife from a household was randomly selected for inclusion, we included only the youngest eligible wife in the study. In accordance with cultural norms, village guides and RAs first approached the heads of household (if the husbands were not the head of households) in order to receive permission to approach other household members.

To confirm eligibility at baseline, RAs asked the head of household to provide a household roster with relationships and ages. Age was then reconfirmed via surveys with individual AGYW and husbands. At all timepoints, up to three attempts are made to reach the selected participants. At baseline, if the person could not be reached after these three attempts, a replacement was chosen from the original listing based on assignment of the next number in the sequence (i.e., 26, and then 27 if required, etc.). This process continued until 25 eligible couples were enrolled in each village.

At baseline, couples were recruited based on the eligibility of the adolescent wife. Adolescent girls and young women were eligible based on the following criteria: 1) age 13–19 years, 2) married, 3) fluent in Hausa or Zarma (local languages), 4) residing in the village with no plans to move out of the village in next 18 months or to be away from the village for more than 6 months during that period, 5) not currently sterilized (to enable measurement of changes in use of reversible methods of contraception from baseline to follow-up), and 6) providing informed consent.

